## Abstract

**Introduction:**

The clinical syndrome of neonatal sepsis, comprising signs of infection, septic shock and organ dysfunction in infants ≤4 weeks of age, is a frequent sequel to bloodstream infection and mandates urgent antimicrobial therapy. Bacterial characterisation and antimicrobial susceptibility testing is vital for ensuring appropriate therapy, as high rates of antimicrobial resistance (AMR), especially in low-income and middle-income countries, may adversely affect outcome. Ho Chi Minh City (HCMC) in Vietnam is a rapidly expanding city in Southeast Asia with a current population of almost 8 million. There are limited contemporary data on the causes of neonatal sepsis in Vietnam, and we hypothesise that the emergence of multidrug resistant bacteria is an increasing problem for the appropriate management of sepsis cases. In this study, we aim to investigate the major causes of neonatal sepsis and assess disease outcomes by clinical features, antimicrobial susceptibility profiles and genome composition.

**Method and analysis:**

We will conduct a prospective observational study to characterise the clinical and microbiological features of neonatal sepsis in a major children’s hospital in HCMC. All bacteria isolated from blood subjected to whole genome sequencing. We will compare clinical variables and outcomes between different bacterial species, genome composition and AMR gene content. AMR gene content will be assessed and stratified by species, years and contributing hospital departments. Genome sequences will be analysed to investigate phylogenetic relationships.

**Ethics and dissemination:**

The study will be conducted in accordance with the principles of the Declaration of Helsinki and the International Council on Harmonization Guidelines for Good Clinical Practice. Ethics approval has been provided by the Oxford Tropical Research Ethics Committee 35-16 and Vietnam Children’s Hospital 1 Ethics Committee 73/GCN/BVND1. The findings will be disseminated at international conferences and peer-reviewed journals.

**Trial registration number:**

ISRCTN69124914; Pre-results.

Strengths and limitations of this studyLittle is known about the current aetiological agents of neonatal sepsis in Vietnam. This prospective study will integrate clinical assessments with microbiological and detailed whole genome sequence data to characterise the aetiology and outcome of neonatal sepsis in this high-mortality setting.This study is being performed at the largest secondary/tertiary paediatrics centre in Southern Vietnam. Data collection at a single site may limit the applicability to other hospitals in the country.Other limitations encountered in designing this study include ethical issues involved in collecting samples from severely ill neonates, lack of current transferable definitions for neonatal sepsis phenotypes and stochastic variations in numbers of cases recruited due to seasonal variation and continuous changes in community antimicrobial and vaccine use.Some contamination of blood cultures is unavoidable in our setting and therefore accurately classifying some isolates as true pathogens in certain cases may be challenging.

## Background

Neonatal sepsis is widely recognised as a clinical syndrome of systemic inflammation in response to, or occurring the same time as, a possible or proven infection (frequently by identifying bacterial bloodstream infection) occurring in children ≤28 days of age. A consensus definition of neonatal sepsis has remained a challenge.^1^ Globally, the incidence of neonatal sepsis is estimated to be 1–5 cases/1000 live births but is lower in full-term neonates (1–2 cases/1000 live births), in whom the incidence is higher in men than women.^2 3^ Early-onset sepsis is defined as the start of sepsis symptoms within 72 hours of birth^1 4^ and is often caused by vertical transmission of pathogens during delivery as a result of chorioamnionitis or maternal genital tract colonisation.^5^ Late-onset sepsis, occurring after 72 hours from birth,^1 6^ may be caused by similar vertical transmission or horizontal transmission mechanisms due to direct contact with the surrounding environment, attendant healthcare staff or any invasive procedures.^7^

### Neonatal sepsis in Southeast Asia

Neonatal sepsis remains a leading cause of neonatal hospital admission, morbidity and mortality in low-income and middle-income countries (LMICs).^8^ In this setting, bacterial infection, including bacteraemia, is complicated by multidrug resistance, particularly related to healthcare acquired infection, and effective management of neonatal sepsis is increasingly problematic.^8^ Recently, WHO has acknowledged the problem of antimicrobial resistance (AMR) as an endemic and widespread problem in LMICs.^9^ In many LMICs untreatable bacterial infections with broadly AMR pathogens are no longer a threat but a common reality. AMR in LMICs represents one of the biggest threats to global health and are one of the greatest current challenges in infectious disease research.

While AMR is an issue with all types of bacterial infection, the issue is most acute in management of clinical sepsis. This is a particular problem in neonates due to high mortality/morbidity rates and the timely need for rapid detection and treatment of the causative pathogen. Sepsis demonstrates extensive geographical diversity in both aetiology and proportions of AMR bacteria isolated.^10 11^ Understanding the local and regional epidemiology of sepsis in hospitalised neonates is crucial in the development of rational management and treatment guidelines, especially in high-risk AMR LMICs locations like Vietnam.

### Sepsis and AMR in Vietnam

Bacterial sepsis is classified into two major groups according to place of acquisition. Hospital-acquired sepsis is defined in patients with clinical manifestations of sepsis and a confirmatory blood culture collected >48 hours following hospital admission.^12^ Hospital-acquired sepsis is a major threat to patient safety, and in locations with poor surveillance and infection control programme such infections are associated with high mortality rates. The incidence of AMR bloodstream infections in Vietnam has increased over recent years and is predicted to increase further.^13^ This trend has comprised an increase in both Gram-negative and Gram-positive pathogens, chiefly *Escherichia coli, Klebsiella pneumoniae, Acinetobacter baumannii, Staphylococcus aureus* and enterococci.

Community-acquired sepsis is also an important cause of fever among patients admitted to hospitals across South and Southeast Asia. In our practice, community-acquired sepsis is defined as the presence of sepsis with a confirmatory blood culture collected within 48 hours after hospital admission.^14^ Distinguishing bacterial infections from other common causes of fever, such as malaria or dengue, can be challenging without diagnostic laboratory support.^15^ Important causes of community-acquired bloodstream infection (CA-BSI) in LMICs include *Salmonella* serovars Typhi and Paratyphi A, *E. coli*, *K. pneumoniae*, *S. aureus* and *Streptococcus pneumoniae*. We have reported increasing levels of AMR in these common community-acquired pathogens and highlighted the difficulties of accurate diagnosis with traditionally available diagnostics. For example in Nepal and Vietnam antimicrobial resistance in *Salmonella* Typhi and *Salmonella* Paratyphi A has severely restricted the options available for antimicrobial treatment.^16^

### Changing aetiology of BSI in Vietnam

The aetiology of CA-BSI in Vietnam has changed considerably over the 20 years. A previous study documented the decline of *Salmonella* Typhi from 2002, the predominant pathogen until this point and the subsequent increase in non-typhoidal *Salmonella* and other opportunistic HIV-associated pathogens.^17^ This shift is likely to reflect a changing landscape of infectious disease related to the HIV epidemic, urbanisation and secondary social determinants within Vietnam. Vietnam, as with many countries in Asia, is undergoing a rapid economic transition, and programmes to improve sanitary conditions have reduced the overall risk of waterborne infections. HIV-associated opportunistic pathogens have now emerged as the leading cause of bloodstream infections and the primary cause of mortality in hospitalised adult patients in this location. These studies were performed at the Hospital for Tropical diseases in Ho Chi Minh City and thus included mainly adults, including those with HIV, and children but not neonates.^18–20^ Therefore, these observations may not be fully representative of the situation in neonates.

### Knowledge gaps

Little is known about contemporary antimicrobial susceptibility patterns and their underlying genetic determinants in the major causes of neonatal bacterial of sepsis in Vietnam. Furthermore, the impact of antimicrobial susceptibility and other virulence factors on disease progression and outcome in neonates in LMICs is also not well documented. To address these issues, we aim to investigate the aetiology of pathogens associated with bacterial sepsis in neonates and to detail the effects of reduced antimicrobial susceptibility on the outcome of sepsis in neonates. This will be a clinical and microbiology laboratory research project between Children’s Hospital 1 and the Oxford University Clinical Research Unit (OUCRU) in Vietnam. This study will be a conduit for introducing molecular biology for bacteriology into routine hospital care at this children’s hospital and will lead to future studies investigating appropriate empirical treatment for bacteraemia and the impact of antimicrobial resistance on the outcome of sepsis in the paediatric and neonatal population in Vietnam.

### Rationale, aim and objectives

To understand the causes of neonatal sepsis and to best inform antimicrobial treatment regimes in our setting, we will perform a prospective observational study at Children’s Hospital 1 in Vietnam from 2017 to 2019. There are limited contemporary data on the causes of bacterial sepsis in neonates in Vietnam. We hypothesise that there have been recent increases in multidrug resistant Gram-negative bacteria causing sepsis in this high-risk group and that methicillin-resistant *S. aureus* has emerged as an important pathogen. We further aim to investigate the clinical features, major causes of neonatal sepsis and the distribution of pathogens by departments, their antimicrobial susceptibility patterns and the genomic profiles of the isolated bacteria as well as their association with disease outcomes.

### Primary objectives

To describe the clinical characteristics of neonates with sepsis, including community and hospital-acquired sepsis, early-onset and late-onset sepsis.To determine the aetiology of neonatal sepsis and the distribution of pathogens by clinical departments including the Neonatology Department and the Neonatal Intensive Care Unit.To determine the antimicrobial susceptibility profiles of the bacteria causing neonatal sepsis and the AMR profiles occurring in community and hospital-acquired infections.To analyse the impact of specific bacteria and AMR profile on the outcomes (mortality, length of stay and cost of treatment) of neonates with sepsis.To determine the genome sequences of bacterial strains associated with neonatal sepsis.

### Secondary objectives

To determine the AMR profiles and gene distribution of isolated bacteria by clinical departments to add insight into the circulation of bacteria associated with hospital acquired infections.To study the genes catalysing resistance to antimicrobials commonly used to treat neonatal sepsis (specifically third/fourth generation cephalosporins, fluoroquinolones and carbapenems).

## Methods

### Study design

This protocol describes a prospective, non-interventional, observational study to characterise the clinical features of neonates with sepsis at Children’s Hospital 1 in Ho Chi Minh City in Vietnam between 2017 and 2019, the microbial population structure, antimicrobial susceptibility patterns and the AMR genes of the bacteria causing that sepsis. All organisms isolated from blood will be stored and archived for molecular characterisation.

### Study site

Children’s Hospital 1 (Neonatology Department, Neonatal Intensive Care Unit, Microbiology Department) is in Ho Chi Minh City in Vietnam. The estimated population of the city was 8.4 million in 2016, and 23.8% are children 0–14 years of age.^21^ Children’s Hospital 1 is the largest tertiary paediatrics centre in Southern Vietnam with 1400 inpatient beds and >1600 staff members. The hospital receives ~1.5 million outpatient visits and 95 000 admissions each year. Care is provided to all children <15 years old from Ho Chi Minh City and other provinces of Southern Vietnam. The neonatal centre at this hospital currently has 120 inpatient beds for the neonatology department and additional 30 beds in the neonatal intensive care unit. The overall mean rate of positive blood cultures in our hospital is 7% per year.

## Definitions

### Definition of sepsis

A sepsis episode in this study is defined as isolation of a clinically relevant pathogen from ≥1 blood culture, drawn from a neonate with ≥1 clinical or laboratory sign of sepsis (table 1).^22^

**Table 1 T1:** Clinical and laboratory signs of neonatal sepsis

Clinical signs of sepsis	Abnormal body temperature (core temperature >38.5°C or <36°C and/or temperature instability); Cardiovascular instability (bradycardia (mean heart rate <10th percentile for age in the absence of external vagal stimulus, beta blockers or congenital heart disease or otherwise unexplained persistent depression over a 0.5–4 hour time period) or tachycardia (mean heart rate >2 SD above normal for age in the absence of external stimulus, chronic unexplained persistent elevation over a 0.5–4 hour time period) and/or rhythm instability, reduced urinary output (<1 mL/kg/hour), hypotension (mean arterial pressure <5th percentile for age), mottled skin, impaired peripheral perfusion); Respiratory instability (apnoea episodes or tachypnoea episodes (mean respiratory rate >2 SD above normal for age) or increased oxygen requirements or requirement for ventilator support); Gastrointestinal (feeding intolerance, poor sucking, abdominal distension); Skin and subcutaneous lesions (petechial rash, sclerema); Non-specific (irritability, lethargy, hypotonia).
Laboratory signs of sepsis	White cells <4×10^9^ cells/L or >20×10^9^ cells/L Immature to total neutrophil ratio (I/T) >0.2 Platelet count <100×10^9^/L C reactive protein>15 mg/L or procalcitonin ≥2 ng/mL Glucose intolerance (hyperglycaemia (blood glucose >180 mg/dL or 10 mmol/L) or hypoglycaemia (blood glucose <45 mg/dL or 2.5 mmol/L)) Metabolic acidosis (base excess <–10 mEq/L or serum lactate >2 mmol/L)

### Diagnosis of neonatal sepsis

Systematic guidelines concerning which patients should have blood cultures performed are not strictly defined in our hospital, although blood culture results are used to confirm the diagnosis of sepsis in neonates with a compatible clinical presentation. We use the criteria suggested by the European Medicines Agency in 2010 for the diagnosis of ‘probable sepsis’ and ‘confirmed sepsis’ in neonates^22^:Probable sepsis: ≥2 clinical and ≥2 laboratory signs;Confirmed sepsis: ≥1 positive culture of a pathogen and ≥1 clinical or laboratory sign.

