## Sample size

In this prospective observational study, we aim to recruit all patients with available data who fulfil the inclusion criteria and are admitted to Children’s Hospital 1 in Ho Chi Minh City in Vietnam from 2017 to 2019. Based on retrospective surveillance data, we estimate recruitment of 800 participants during the study period. Blood cultures will be performed in all cases, we expect to yield ~400 bacterial isolates.

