## Analysis plan

### Statistical comparisons

Data will be presented in the form of tables and bar charts for descriptive variables, that is, number of organisms per year and number of AMR organisms per year. Statistical comparisons of features between groups (positive/negative blood culture, Gram-negative/Gram-positive bacteria, survival/non-survival, etc) and time trend analysis of the cultured isolates by month and the antimicrobial susceptibility patterns will be conducted. These data will be placed in the context of the broader population by comparison of these data with historical laboratory records of pathogens isolated from patients with bloodstream infections. Historical data from both neonates and older children will be analysed descriptively, and where appropriate, time trend analyses will be performed to determine significant alterations in bloodstream infection aetiology. All statistical analysis will be performed using Stata V.14 and R. P values of ≤0.05 will be considered significant.

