## Discussion

As a conduit for introducing molecular biology for bacteriology into routine hospital care in Vietnam, the study is unique and is planned to lead to future studies investigating appropriate empirical treatment for bacteraemia and the impact of AMR on the outcome of sepsis in the neonatal and paediatric population in Vietnam. By studying and defining disease aetiology, antimicrobial susceptibility patterns and disease outcome, we plan to develop an improved approach to managing bloodstream infections in our setting, and we will use these data to initiate intervention studies focused on preventing sepsis with AMR pathogens in neonates. Table 2 shows the summary of this study.

**Table 2 T2:** Study summary

Title	The clinical features, antimicrobial susceptibility patterns and genomics of bacteria causing neonatal sepsis in a children’s hospital in Vietnam
Design	Observational prospective study All organisms isolated from blood will be stored and archived for molecular characterisation
Participants	Neonates (≤1 month of age) with sepsis
Planned enrolment period	2017–2019
Primary objectives	To investigate the clinical characteristics of neonatal sepsis; To define the aetiology, the percentage of positive blood culture and major causes of sepsis; To investigate the antimicrobial susceptibilities of the pathogens causing sepsis and the rate of antimicrobial resistance; To measure the impact of sepsis on the severity of disease and the outcomes (mortality rate, length of stay and cost of treatment) of hospitalised neonates; To analyse the genome sequences of bacterial strains causing neonatal sepsis.
Secondary objectives	To analyse the antimicrobial resistance profiles and gene distribution by clinical departments to add insight into the circulation of bacteria causing nosocomial infections; To study the genes catalysing resistance to the antimicrobials commonly used to treat neonatal sepsis (specifically third-generation/fourth-generation cephalosporins, fluoroquinolones and carbapenems).

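### Culture-positive and culture-negative neonates enter under different sign thresholds, so the percentage of positive cultures and the positive/negative comparison of features partly reflect the entry rule

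*Protocol article*

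**What the plan says.** The inclusion criteria of the protocol article admit neonates diagnosed with either probable or confirmed sepsis, provided that a blood culture was taken. The section Diagnosis of neonatal sepsis sets the two thresholds: "Probable sepsis: ≥2 clinical and ≥2 laboratory signs;Confirmed sepsis: ≥1 positive culture of a pathogen and ≥1 clinical or laboratory sign".

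Two stated analyses depend on culture result:

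- Table 2 (study summary) gives as a primary objective "To define the aetiology, the percentage of positive blood culture and major causes of sepsis". The fuller list under Primary objectives does not mention this percentage.
- The section Statistical comparisons plans "Statistical comparisons of features between groups (positive/negative blood culture, Gram-negative/Gram-positive bacteria, survival/non-survival, etc", with P values of 0.05 or less called significant.

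The section Definition of sepsis adds: "A sepsis episode in this study is defined as isolation of a clinically relevant pathogen from ≥1 blood culture", drawn from a neonate with at least one sign.

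The article names no common sign threshold for the positive/negative analyses, and its list of limitations does not mention the difference in entry rules.

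**The concern.** The culture result decides how many signs a neonate needs to be enrolled. A culture-positive neonate with one or two signs is kept, and an equally mild culture-negative neonate is never enrolled. Sign burden is thus tied to culture status by the selection rule, before biology plays any part.

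Two readings of the results are at stake. The percentage of positive cultures may be taken as the yield of blood culture in suspected neonatal sepsis, when it is partly a product of who was let in. A difference in clinical or laboratory features between the two groups may be taken as a feature of bacteraemia, when some of those features are the very signs used for selection.

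There is a related conflict of definition. If a sepsis episode requires an isolate, the probable cases enrolled without a cultured pathogen are not sepsis episodes, although Table 2 describes all participants as neonates with sepsis. It is then unclear which denominator applies to statements about sepsis.

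**Working it through.** **Inputs.** From Diagnosis of neonatal sepsis: without a cultured pathogen, at least 2 clinical and 2 laboratory signs (2 + 2 = 4 or more); with one, at least 1 sign of either kind. From Sample size: 800 participants and about 400 isolates. Not given, so assumed: *q*, the share of enrolled culture-positive neonates who also meet the 2+2 rule.

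**The plan's own figure.** 800 and about 400 are said to rest on retrospective surveillance data. No precision or power formula is given, so none can be reproduced. Only the ratio 400/800 = 50% can be formed. It relates isolates to participants; reading it as 400 positive and 400 negative neonates is an assumption made here for illustration.

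**Direction.** Let *P* and *N* be the enrolled culture-positive and culture-negative neonates.

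- As enrolled: *P*/(*P* + *N*).
- At a common strict (2+2) threshold: *qP*/(*qP* + *N*), which is lower whenever *q* < 1.
- At a common lax (one-sign) threshold: *P*/(*P* + *N*/*r*), where *r* is the share of culture-negative neonates with at least one sign who meet 2+2. This is also lower whenever *r* < 1, but it cannot be computed from the study, because the mild culture-negative neonates are not enrolled.

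Against either common threshold, the enrolled percentage is too high.

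**Size at the common strict threshold**, with *P* = *N* = 400, so that the percentage positive is 400*q*/(400*q* + 400):

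| *q* (assumed) | Positives meeting 2+2 | Percentage positive |
|---|---|---|
| 1 | 400 | 400/800 = 50.0% |
| 0.9 | 360 | 360/760 = 47.4% |
| 0.75 | 300 | 300/700 = 42.9% |
| 0.5 | 200 | 200/600 = 33.3% |
| 0.25 | 100 | 100/500 = 20.0% |

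**Signs.** By rule, 0% of enrolled culture-negative neonates fall below 2+2. Among culture-positive neonates the share is 1 − *q*: 10%, 25% and 50% at *q* = 0.9, 0.75 and 0.5. That contrast arises even if culture status has no relation to signs.

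**What is untouched.** Gram-negative versus Gram-positive, species and resistance-profile comparisons are made among neonates with a cultured pathogen, who all enter under a rule that requires only one sign. The unequal threshold does not distort them.

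**Definitions side by side.** The definition of a sepsis episode is in substance the criterion for confirmed sepsis. The inclusion criteria add probable sepsis. Both cannot define sepsis in this study.

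**The case against.** The strongest defence is one of proportion. The two categories are attributed to European Medicines Agency criteria, and using them for diagnosis is a recognised choice. The percentage positive appears only in the summary table, and the positive/negative contrast is one example in a parenthesis. The main aims (aetiology, susceptibility, the effect of specific bacteria and resistance on outcome, genomes) rest on culture-positive neonates or their isolates. A full analysis plan may hold adjustment or restriction, and a severity score is collected. Most of this stands, and it lowers the severity. It does not remove the point: the entry rule, the objective and the comparison are all fixed in this text, and taken together they give a distorted percentage and a distorted comparison of signs.

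Three stronger readings are tempting and are not supported.

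- A reader might set "The overall mean rate of positive blood cultures in our hospital is 7% per year" against "Blood cultures will be performed in all cases, we expect to yield ~400 bacterial isolates" and conclude that 7% versus 50% shows the effect of selection. The 7% covers the whole hospital, which treats all children under 15, and the 400 counts isolates. The gap proves nothing about this rule.
- A reader might infer a biased mortality ratio between culture-positive and culture-negative neonates. The article ties its outcome analyses to bacteria, genome composition and resistance; it names no mortality contrast by culture result. Any such ratio would also need a model of death by sign count that the article does not supply.
- A reader might infer that culture-negative neonates must look sicker. The rule pushes that way, but if bacteraemia itself produces more signs, the observed difference could still go in the other direction.

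**Conclusion.** The point holds, at moderate severity. The percentage of positive cultures and the positive/negative comparison of clinical and laboratory features partly reflect the entry rule. The direction of the push follows from the text alone; it disappears for the strict-threshold percentage only if every culture-positive neonate also meets the 2+2 rule.

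The size is not known. It ranges from about 3 percentage points (50.0 − 47.4 = 2.6) at a share of 0.9 to about 17 (50.0 − 33.3 = 16.7) at 0.5, assuming equal groups of 400 neonates. The conflict between the sepsis-episode definition and the inclusion criteria is a smaller matter of labelling, but the two sections must be reconciled.

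**What to change.** In Statistical comparisons, report the percentage of positive cultures and all positive/negative comparisons among neonates who meet at least 2 clinical and 2 laboratory signs, whatever the culture result. Show confirmed cases below that threshold in a separate column. Where a percentage among all enrolled neonates is given, describe it as an enrolment mix and not as a culture yield.

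Reconcile Definition of sepsis with the inclusion criteria, for example by labelling the former as the definition of a confirmed sepsis episode, and state for each objective whether the denominator is confirmed cases or all enrolled.

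The cost is low. Recruitment and care do not change, and the article already provides for collecting clinical and laboratory data. There are two downsides. Confirmed cases with few signs leave this one set of comparisons. And because a confirmed case needs only one sign to enter, some Table 1 signs may not have been measured in those neonates; unmeasured signs should be treated as missing and not counted as absent, or culture-positive neonates will be wrongly placed below the threshold.
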